#### Secondary Outcomes

The study has three secondary clinical efficacy end-points:

The modified Rankin scale (mRS) will be used to evaluate the subjects’ degree of disability. We will record the ratio in each group with mRS scores 0–5, and the proportion of subjects with mRS ≤1 in each group. Comparisons will be made on day 28 (immediately after treatment) and day 90 after IS onset, and statistical analysis will be conducted between groups.The activity of daily living (ADL) scale will be measured with the Barthel Index (BI). The differences of BI scores (before and 28 days after treatment, and 90 days after onset) will be compared within and between the groups, and the proportion of participants with BI scores ≥90 will be recorded.TCM symptom scores will be used to quantitatively score the symptoms. The differences in TCM symptom scores between groups will be compared for baseline and 28 days after treatment and 90 days after onset, and the differences between groups will be calculated. The comprehensive curative effect criteria are as follows: i) clinically resolved: symptoms and signs disappear or largely decrease, syndrome score decrease by ≥95%; ii) significant effect: symptoms and signs are significantly improved, syndrome score decrease by ≥70%; iii) effective: symptoms and signs are improved, syndrome score reduced by ≥30%; and iv) no effect: no significant improvement or even aggravation of symptoms and signs, <30% reduction of syndrome score (Jin et al., 2019). The formula for evaluation (nimodipine method) is:$$\text{comprehensive curative effect}=\frac{\text{integral before treatment}-\text{integral after treatment}}{\text{integral before treatment}}\times 100\%.$$

The number of total effective cases including clinically resolved cases, significant effect cases, and effective cases (i–iii).

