### Inclusion Criteria

Patients will be recruited for this study if they meet all of the following criteria: (1) 40 ≤ age ≤ 80 years, (2) consistent with the western and Chinese medicine diagnostic criteria of IS, (3) meet the diagnostic criteria of TCM symptom differentiation (QDBS syndrome), (4) imaging (computed tomography or magnetic resonance imaging) confirmed anterior circulation infarction (Oxfordshire Community Stroke Project clinical classification of complete or partial anterior circulation infarction), (5) course of disease of 1–4 weeks, (6) 4 ≤ National Institute of Health Stroke Scale (NIHSS) score ≤ 20, (7) first attack or previous history of cerebral infarction but without disability before this attack (modified Rankin Scale [mRS] score ≤1), and (8) signed informed consent.

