### Statistical Analysis Plan

Statistical analysis will be performed using SPSS version 15.0 for Windows (Chicago, IL, USA). Professional statisticians who are independent of all the other processes of the study will perform the statistical analyses. Consistent with the CONSORT statement and intention to treat principle, the last observation carried forward method will be used for missing values. Cases in the per protocol set (PPS) are those who thoroughly adhere to the protocol without absence of baseline characteristics. Analyses of the primary outcome and curative effect will be carried out using a full analysis set approach and PPS approach. The safety analysis set will include all randomized patients who have completed at least one study visit. Participating centers will be required to count the number of participants in each center and list those who are removed from the PPS. For quantitative data, we will calculate the mean, standard deviation, median, minimum, maximum, lower quartile (Q_1_), upper quartile (Q_3_); and for qualitative data, we will describe numbers and percentages. Inter-group comparisons will be analyzed by appropriate methods: independent t-tests (homogeneity of variance, normal distribution) or Wilcoxon rank-sum test for quantitative data, chi-square test or Fisher’s exact test (if chi-square test is not applicable) for qualitative data, and Wilcoxon rank-sum test or Cochran-Mantel–Haenszel test for ranked data. *P* <0.05 will be considered statistically significant.

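### The mRS is recorded only as 0–5 and carry-forward has no exception for death, so a patient who dies is either unscored or may keep a living disability score

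*Protocol article*

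**What the plan says.** All references are to the protocol article.

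- **Secondary Outcomes, mRS:** "We will record the ratio in each group with mRS scores 0–5", together with "the proportion of subjects with mRS ≤1 in each group". On timing: "Comparisons will be made on day 28 (immediately after treatment) and day 90 after IS onset".
- **Secondary Outcomes, Barthel Index:** score differences are compared at 28 days after treatment and 90 days after onset, and "the proportion of participants with BI scores ≥90 will be recorded".
- **Statistical Analysis Plan:** under the intention-to-treat principle, "the last observation carried forward method will be used for missing values". On analysis sets: "Analyses of the primary outcome and curative effect will be carried out using a full analysis set approach and PPS approach".
- **Inclusion Criteria:** severity at entry is "4 ≤ National Institute of Health Stroke Scale (NIHSS) score ≤ 20", 1–4 weeks after onset, age 40–80.

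Neither Secondary Outcomes, Table 3 nor the Statistical Analysis Plan section says how a death is scored on the mRS or the BI. Deaths would be recorded through the safety route (Safety and AE Monitoring; Table 3 marks adverse-event recording at V2 and V4).

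**The concern.** The two printed rules do not fit together when a patient dies. A scale that stops at 5 gives a death no value. The only stated rule for an absent value is LOCF, and nothing exempts death from it. The plan therefore leaves two outcomes for a patient who dies before day 90 after onset: no mRS at all, or a score observed while alive.

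Both fail to treat death as the worst state on a disability scale. The second can go further and place a dead patient among those with mRS ≤1 or BI ≥90. At stake is the comparison of disability between arms at day 28 and day 90. If deaths are unevenly spread, the arm with more of them is not marked down on these outcomes. With 32 patients in three of the four arms, one or two deaths are visible in a percentage.

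This goes beyond detail left to an analysis plan that is not shown. The article prints the range 0–5 and the carry-forward rule itself, and an analysis plan or CRF that follows them would inherit the gap.

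**Working it through.** **1. Arm sizes (Sample Size Estimates).** 160 split 1:2:1:1 gives 160 × 1/5 = 32 for BHG, YTG and placebo, and 160 × 2/5 = 64 for NXTC. This matches the article.

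**2. Is there time for a death between the day-28 visit and day 90?** Inputs: entry 1–4 weeks (7–28 days) after onset, screening up to 7 days, V2 at day 28 ± 4 (Table 3).
- Earliest V2: 7 + 24 = 31 days after onset. Time left: 90 − 31 = 59 days.
- Latest V2: 28 + 7 + 32 = 67 days after onset. Time left: 90 − 67 = 23 days.

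So 23 to 59 days remain before day 90 after onset.

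**3. What the printed rules give, by time of death.**

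| Time of death | Unscored reading | Carry-forward reading | False mRS ≤1 success? |
|---|---|---|---|
| Before V2 | No day-28 or day-90 mRS | V1 score at both times | Only if V1 mRS is 0–1; unlikely at NIHSS ≥4 |
| After V2, before day 90 | No day-90 mRS | Day-28 score used at day 90 | Yes, if the day-28 mRS was 0–1 |

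The BI follows the same pattern, with a last value of 90 or more as the condition. The mRS limit in the inclusion criteria ("without disability before this attack (modified Rankin Scale [mRS] score ≤1") describes the state before the stroke, so it is not the V1 score that would be carried.

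**4. Size per affected death, carry-forward reading.** Counting one death as a success rather than a failure, with the denominator unchanged, shifts the proportion by 1/n:
- 1/32 = 3.1 points (BHG, YTG or placebo); 1/64 = 1.6 points (NXTC).
- Two such deaths in one arm: 2/32 = 6.3 points, or 2/64 = 3.1 points.

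**5. Size per death, unscored reading.** If the dead patient is dropped, s successes out of n become s/(n − 1), a rise of p/(n − 1) with p = s/n. The article gives no p. For an assumed p of 20–40% this is 0.20/31 to 0.40/31 = 0.6 to 1.3 points in a 32-patient arm, and 0.20/63 to 0.40/63 = 0.3 to 0.6 points in NXTC.

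**6. How many patients?** The article gives no mortality rate. Assume 1–4% by day 90: 160 × 0.01 = 1.6 to 160 × 0.04 = 6.4, so about 2–6 deaths. Under carry-forward all of these are mis-scored on the ordinal mRS, because a living score replaces the worst category. Fewer are false mRS ≤1 successes. If 0–40% of those who die had a last score of 0–1 (also an assumption), that is 0 to 6.4 × 0.40 = 2.6 patients in the whole trial. The expected inflation in an arm is then 0 to 4% × 40% = 1.6 points.

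**The case against.** The strongest counter-argument is that the carry-forward step is an inference. The article never calls a death a missing value and never says that scores are carried past death. The abstract refers to a predefined analysis plan, not shown here, which could exempt deaths. The inference point stands, and the finding is worded accordingly. It does not remove the problem: without LOCF the patient has no mRS, and death is still not counted as the worst outcome. Nor does a possible later exemption alter the printed 0–5 range.

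A reader might infer that 2–6 of 160 patients would be falsely counted as successes. The documents do not support that. The figure is an assumed number of all deaths; a patient who dies with a last mRS of 2–5 is already a failure for mRS ≤1. The lower bound for false successes is zero.

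A reader might also infer that the trial ignores deaths altogether. It does not: they fall under serious adverse events. The gap is that the safety record does not feed into the disability outcomes.

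The population also limits the number of deaths. Entry is 1–4 weeks after onset, and the exclusions cover large infarcts with unstable vital signs, cerebral hemorrhage and other serious organ disease. For BI ≥90 the article says only that the proportion is recorded and names no test. These points reduce the expected size and leave the rule as it is.

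**Conclusion.** The point holds in a limited form. The printed mRS range and the unqualified LOCF rule leave a death either unscored or, if it is handled as missing, scored as alive. A false day-90 success is realistic mainly for a death between V2 and day 90 in someone who had reached mRS 0–1 or BI ≥90. Each one is worth up to 3.1 points in a 32-patient arm and 1.6 points in NXTC.

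The overall effect is probably small. On assumed mortality of 1–4%, and with 0–40% of those who die having a last mRS of 0–1, the expected inflation is 0 to 1.6 points per arm. Both ranges are assumptions, since the article supplies neither figure. The outcomes are secondary and the study calls itself a pilot. The change is worth making because it costs almost nothing and needs to be settled before unblinding; it does not threaten the trial's main result.

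**What to change.** - Record the mRS as 0–6 with death = 6. Show category 6 in the distribution and include it in the between-group test.
- Count deaths as failures for mRS ≤1 and BI ≥90, with the full analysis set as denominator.
- State that LOCF is not applied after death. For BI as a score, name a convention in advance, for example the worst score or worst rank. Setting BI to 0 is one option among several.

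Cost: one CRF code and two or three lines of analysis wording. If data collection has begun, deaths can be coded from the serious-adverse-event records before unblinding. Neither the sample size of 160 nor the primary endpoint (NIHSS change at day 28) is altered.

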#### Specific Indicators

Ten subjects per group will be randomly selected and blood and urine samples will be taken for specific indicator examination to explore the therapeutic biomarkers and pharmacodynamic material basis of PSC in treating patients with IS (QDBS syndrome). The study has three categories of specific indicators:

Biological indicators: including tissue-type plasminogen activator (t-pa), plasminogen activator inhibitor type 1 (PAI-1), D-dimer, interleukin-1 (IL-1), IL-6, tumor necrosis factor-alpha (TNF-α), high-sensitivity C-reactive protein (hs-CRP), matrix metallo proteinase-9 (MMP-9), platelet aggregation rate, endothelin, nitric oxide (NO), adenosine triphosphate (ATP), superoxide dismutase (SOD), glutathione peroxidase (GSH-PX), malondialdehyde (MDA), and peroxidase (POD).Metabolomic indicators (blood and urine samples): gas chromatography–mass spectrometry (GC–MS), liquid chromatography-mass spectrometry (LC–MS), and other technologies will be used to reveal the chemical and biological fingerprints, screen effective components, and explore the possible metabolic pathways and target molecules of BHG, NXTC, and YTG for treating IS with QDBS.Proteomics (blood samples): two-way fluorescence differential gel electrophoresis (2D-DIGE) will be used to assess the proteome of each group before and after intervention. Matrix-assisted laser desorption/ionization time-of-flight/time-of-flight mass spectrometry (MALDI TOF/TOF MS) techniques will be used to identify the differentially expressed proteins. Bioinformatics analyses will be performed to assess the biological functions of differentially expressed proteins, and STRING and Ingenuity Pathway Analysis will be used to establish the protein network affected by BHG, NXTC, and YTG.

Blood sample collection requirements: subjects fast 10 h before each collection, 5 ml blood is drawn and centrifuged, and the serum stored in Eppendorf tubes at −70 °C. Urine sample collection requirements: subjects fast 10 h before taking medicine (allow to drink water), fast and water prohibit 1 h before urine collection to 2 h after taking medicine, ration water at 200 mL/h for 2–8 h after taking medicine, and consume a low-fat meal 4 h after taking medicine. Urine samples will be collected at baseline and after treatment (28 days) and stored in Eppendorf tubes at −70 °C.

To guarantee the consistency of the laboratory tests, the proteomics and metabolomics experiments will be carried out in a centralized lab. This pilot study is designed to precisely identify biomarkers of IS with QDBS syndrome and the bioactive constituents of BHG, NXTC, and YTG related to PSC.

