### Randomization and Blinding

Central randomization will be performed using stratified and permuted blocks. According to the randomized clinical study program, with the help of the SAS 9.4 statistical software package PROC PLAN process, a stratified randomization method will be adopted to list the random coding table and generate the random arrangement of subjects’ treatment. Patients will be randomized in blocks of varying sizes within each center and stratified by centers.

All eligible participants will be randomly divided into the experimental group 1 (BHG group), experimental group 2 (NXTC group), experimental group 3 (YTG group), and placebo control group using a 1:2:1:1 ratio. According to the randomized clinical study program, the randomized code of the trial drug by statistical experts is the unique identification code of participants. Considering that the dosage forms include granules and capsules, a double-blind and double-simulation design will be adopted. All the participants, researchers, research assistants (conducting interviews with the participants), laboratory and inspection staff, and statisticians will be blinded to treatment assignment until the study is completed.

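### The only proteomic contrast named is before versus after within each group, yet the protein network is attributed to the three prescriptions; change versus placebo should be stated

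*Protocol article*

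**What the plan says.** Specific Indicators (Outcome Measures) sets up the substudy: "Ten subjects per group will be randomly selected and blood and urine samples will be taken for specific indicator examination". Under Randomization and Blinding there are four arms, the last two being "experimental group 3 (YTG group), and placebo control group using a 1:2:1:1 ratio", so ten placebo patients are among those sampled. Table 3 schedules metabolic and proteome data at V1 (screening) and V2 (day 28 ± 4).

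The proteomic text then runs in three steps:

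1. 2D-DIGE "will be used to assess the proteome of each group before and after intervention".
2. Mass-spectrometry "techniques will be used to identify the differentially expressed proteins".
3. "STRING and Ingenuity Pathway Analysis will be used to establish the protein network affected by BHG, NXTC, and YTG".

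Step 1 gives a before-after comparison by group. Step 2 does not say between what the proteins differ. Step 3 credits the result to the three active prescriptions.

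Inclusion Criteria require a "course of disease of 1–4 weeks", and the Intervention section gives guideline-based basic treatment to every arm.

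**The concern.** Step 3 is a causal statement about three drugs, and the only comparison stated before it is before versus after. In patients one to four weeks after a stroke, re-sampled about four weeks later on basic treatment common to all arms, inflammatory, coagulation and repair proteins may well move without any study drug. A within-arm change therefore has two components, drug effect and natural course, and cannot separate them. A larger sample would not help, because the problem lies in what is estimated and not in its precision.

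At stake is the biomarker objective, which the Abstract and Introduction put among the main aims. If differential expression were judged within arms, recovery markers could enter all three networks. Their similarity could then be taken for a shared mechanism of three similar prescriptions.

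**Working it through.** The article gives no figure for this point, so there is none to reproduce. The check sets the texts side by side and then illustrates the size.

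**Comparison stated for each outcome**

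| Outcome | Comparison named in the article |
|---|---|
| NIHSS (primary) | change from baseline, between groups |
| mRS | between groups |
| Barthel Index | within and between groups |
| TCM symptom score | between groups |
| Proteome | each group, before and after |

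Proteomics stands apart: a comparison is named, but not one between groups.

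**Size if before-after tests alone decided the matter**

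Inputs from the article: 10 patients per group, and the general two-sided 0.05 level. Assumptions, none of them in the article: a paired t-test per protein; no drug effect; the same natural shift *d* in every arm, in SDs of the paired differences; equal variances and independent arms.

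*Within-arm test, n = 10.* The statistic is noncentral t with 9 degrees of freedom and noncentrality *d*√10. The probability of a flag is *p* = P(|T| > t₀.₉₇₅,₉).

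| *d* | *d*√10 | *p*, given arm | 1 − (1 − *p*)³, any of three active arms |
|---|---|---|---|
| 0 | 0 | 0.05 | 0.14 |
| 0.25 | 0.79 | 0.11 | 0.29 |
| 0.5 | 1.58 | 0.29 | 0.65 |
| 0.8 | 2.53 | 0.62 | 0.94 |
| 1.0 | 3.16 | 0.80 | 0.99 |

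*Change versus placebo, 10 against 10.* The common shift cancels (*d* − *d* = 0), so the probability of a false flag is 0.05 for every *d*.

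*Discarding proteins that are also significant in placebo.* This informal rule does not repair the problem. With the same shift in both arms, the probability of significance in a given active arm but not in placebo is *p*(1 − *p*):

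- *d* = 0.5: 0.293 × 0.707 = 0.21
- *d* = 0.8: 0.616 × 0.384 = 0.24
- *d* = 1.0: 0.803 × 0.197 = 0.16

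All are above 0.05, and all are false attributions. The data must be compared as changes, not as a list of significant results per arm.

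**Price of the placebo comparison.** For a true difference δ in change between a prescription and placebo, the statistic is noncentral t with 18 degrees of freedom and noncentrality δ√5. Power is about 0.40, 0.56 and 0.80 for δ = 0.8, 1.0 and 1.32 SD.

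**The case against.** The strongest reply is that step 1 describes measurement, not a test: it says who is assayed and when, in line with Table 3. Each group includes placebo, and differential expression is tied to no contrast at all. The Statistical Analysis Plan section has a general rule for inter-group comparisons, lists two-sample tests and names no paired test. A separate analysis plan is mentioned in the Abstract, and the definition of differential expression may be there. On this view the text fits a placebo-controlled reading.

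Much of this stands. A reader might infer that the plan will read natural recovery as a drug effect; the article does not say so, and nowhere says that placebo data are set aside. The probabilities above likewise describe an assumed test and assumed shifts, not known error rates of this trial.

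What does not stand is that the text needs no change. The general rule does not mention proteomics and does not say whether change or post-treatment level is compared. The point also does not rest on silence alone: a comparison is written down, it is before-after, and a claim about the prescriptions follows it. Nor does sampling placebo settle the matter, since setting lists of significant proteins side by side across arms would still attribute falsely.

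A reader might also extend the criticism to the Barthel Index, whose scores "will be compared within and between the groups". That is not supported. The randomised comparison is stated there, and no efficacy claim is drawn from the within-group one.

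**Conclusion.** The point holds in a limited form. The article names only a within-group before-after contrast for the proteome and attributes the resulting network to the three prescriptions. Followed as written, that contrast mixes drug effect with natural course. A comparison with placebo is neither excluded nor stated.

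If before-after tests alone were used, the chance of flagging an unaffected protein in a given arm would rise from 0.05 to between 0.29 and 0.80 for natural shifts of 0.5 to 1.0 SD. This rests wholly on the assumed test and shifts, as the article gives neither.

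Severity is low. The substudy covers 4 × 10 = 40 of 160 patients, is exploratory and sits in a self-described pilot. The primary outcome compares changes between groups and is untouched.

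**What to change.** In Specific Indicators, define a protein or metabolite as affected by a prescription by the between-group difference in change from baseline: each prescription minus placebo, adjusted for the baseline value. Enter only those proteins into the STRING and Ingenuity network. Report within-group changes as descriptive.

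The cost is wording and analysis only, since placebo samples at V1 and V2 are already scheduled. The downside is that fewer proteins will be declared affected: with 10 against 10, only differences of about 1.3 SD of the change reach 80% power before any gain from baseline adjustment.

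### The stated aim of precisely identifying biomarkers of QDBS stroke goes beyond the design: every patient has QDBS, and ten per arm supports exploration only

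*Protocol article*

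**What the plan says.** Specific Indicators describes the marker substudy twice, in different terms. Where it introduces the sampling it says "Ten subjects per group will be randomly selected and blood and urine samples will be taken for specific indicator examination", and gives the purpose as "to explore the therapeutic biomarkers and pharmacodynamic material basis of PSC in treating patients with IS (QDBS syndrome". Where it closes, it says "This pilot study is designed to precisely identify biomarkers of IS with QDBS syndrome", and adds the bioactive constituents of the three prescriptions. The last paragraph of the Introduction also sets the aim of finding clinical biomarkers related to stroke with QDBS.

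Inclusion Criteria, item 3, requires that all patients "meet the diagnostic criteria of TCM symptom differentiation (QDBS syndrome". Trial Design and Randomization and Blinding list four arms (BHG, NXTC, YTG, placebo), all recruited under that criterion.

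The measurements are a panel of named assays ("Biological indicators: including tissue-type plasminogen activator (t-pa), plasminogen activator inhibitor type 1 (PAI-1), D-dimer, interleukin-1 (IL-1), IL-6" and others), metabolomics in blood and urine, and proteomics in blood, with sampling at baseline and day 28. The one significance rule in the article, in Statistical Analysis Plan, is that P "<0.05 will be considered statistically significant".

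**The concern.** A biomarker of stroke with QDBS, in the sense that matters for syndrome-based treatment, has to distinguish QDBS stroke from stroke without QDBS. A trial that enrols only QDBS patients cannot show this. A claim of precision also implies that effects are estimated tightly enough to tell real markers from noise, and ten patients per arm makes that doubtful.

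The Abstract and Discussion intend the results as an objective basis for precise treatment. If a marker list from 40 patients is reported under the stronger aim, readers may take it as evidence about the syndrome that the design could not have produced. A second risk is that change from baseline to day 28 within an arm is read as a drug effect. Patients enter one to four weeks after onset, when markers may move with recovery alone.

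**Working it through.** **1. Aim against population.** To attribute a marker to the syndrome one needs mean(marker | stroke with QDBS) − mean(marker | stroke without QDBS). Inclusion criterion 3 leaves the second term unobserved. The contrasts that do exist are:
- active arm versus placebo, which is randomised and addresses treatment response within QDBS stroke;
- active arm versus active arm, which addresses differences between prescriptions within QDBS stroke;
- day 28 versus baseline within an arm, which mixes drug effect with recovery.

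None compares QDBS with non-QDBS stroke. This follows from eligibility and does not depend on sample size or on the analysis.

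**2. Precision with ten per arm.** The article states no size calculation for the substudy, so there is no figure to reproduce. Sample Size Estimates concerns NIHSS only. Inputs: n = 10 per arm (Specific Indicators); a two-sided two-sample t-test (Statistical Analysis Plan names independent t-tests or the rank-sum test); α = 0.05.
- 95% CI half-width = t(0.975; 18 df) × √(2/10) = 2.101 × 0.447 = 0.94 SD.
- Power comes from the noncentral t with noncentrality d × √(10/2) = 2.236d.

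| True difference | Power, 10 vs 10 |
|---|---|
| 0.5 SD | 18.5% |
| 0.8 SD | 39.5% |
| 1.0 SD | 56% |
| 1.32 SD | 80% |

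For 80% power at 0.8 SD, 26 per arm would be needed. If the main trial's 20% dropout also applied to the subset (an assumption; no subset attrition is given), 8 versus 8 would have 80% power only at 1.51 SD.

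The SD here is that of the quantity analysed. Adjusting for baseline can make that SD smaller, by an amount that depends on a correlation the article does not give.

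**3. Multiplicity, conditional.** This step applies only if the 5% rule is the sole threshold used for the markers. The section names 16 assays by count: t-PA, PAI-1, D-dimer, IL-1, IL-6, TNF-α, hs-CRP, MMP-9, platelet aggregation, endothelin, NO, ATP, SOD, GSH-PX, MDA and POD.
- Tests: 16 × 3 active-versus-placebo contrasts = 48.
- Expected false positives if no marker responds: 48 × 0.05 = 2.4.
- Chance of at least one: 1 − 0.95^48 = 91% if the tests are independent. Correlated markers would be expected to lower this, but the 2.4 does not change.
- The numbers of metabolomic and proteomic features are not stated. For an assumed 100 to 1000 features, none responding, 5 to 50 false hits per contrast would be expected (100 × 0.05 to 1000 × 0.05).

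**The case against.** The best defence is that the article already frames the substudy as exploratory. Specific Indicators uses that language for the sampling and the pathways, the Discussion uses it for the biological basis, and the trial is called a pilot. The markers are neither primary nor secondary outcomes, so no efficacy conclusion rests on them, and ten per arm is acceptable for generating hypotheses. All of this stands. It reduces the defect to a stated aim that is out of line with its surroundings, but does not remove it: the closing sentence and the Introduction still claim something the design cannot deliver.

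Two stronger readings are tempting and are not supported.
- A reader might infer that the marker tests will run at 5% with no error control. Statistical Analysis Plan never mentions the biomarkers or the omics data, Specific Indicators gives no criterion for differential expression, and the Abstract refers to a predefined analysis plan that is not shown. Error control may well be set there, so the false-positive counts are conditional.
- A reader might infer that the marker list will be mostly chance findings and natural recovery. Placebo patients are sampled too, so recovery can be separated from drug effect. Naming two sampling times does not commit the trial to within-arm tests. The share of hits that are false depends on how many markers truly respond, which is unknown.

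**Conclusion.** The concern holds as an overstated aim. The missing non-QDBS comparator is decisive: it rests only on the inclusion criterion and the list of arms, and no analysis plan could repair it. The precision claim fails on the numbers in the table, which assume a two-sample t-test and no attrition in the subset. Multiplicity adjustment would not rescue it, because a stricter threshold makes the detectable difference larger. The multiplicity figure is supporting evidence only, subject to the condition stated with it.

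The consequence is confined to the biomarker aim. The NIHSS comparison, the secondary outcomes and safety are unaffected. The change is worth making because the marker results are meant to guide treatment and the correction costs almost nothing.

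**What to change.** 1. Bring the closing sentence of Specific Indicators, and the matching aim in the Introduction, into line with the exploratory wording already used. Suggested text: the substudy will explore candidate markers of treatment response within ischemic stroke with QDBS; findings are hypothesis-generating and cannot distinguish QDBS from other stroke.
2. State that marker conclusions rest on the randomised comparison of change versus placebo, adjusted for the baseline value, and not on before/after change within an arm.
3. If no other threshold is set elsewhere for the markers, add false-discovery-rate control within each platform (named assays, metabolomics, proteomics), for example by Benjamini-Hochberg. If the analysis plan already sets one, a cross-reference is enough.

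No extra patients, samples or assays are needed. The cost is a more modest stated aim and fewer nominally significant markers.
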